## Study Design/Methodology

We have chosen an individual-level response adaptive randomized platform study design along with a pragmatic, mixed-methods approach to compare five RPM program configurations for delivering post-acute monitoring to patients with sepsis or lower respiratory tract infection across western and central Pennsylvania.

## Study Setting

Participants will be recruited from the hospitals listed below. All hospitals are located in Pennsylvania. Historical data suggests that recruiting from these hospitals will allow us to reach our target sample size. For detailed recruitment methods, please refer to the Recruitment Plan

| Recruitment Sites                  |                             |                     |
|------------------------------------|-----------------------------|---------------------|
| Armstrong County Memorial Hospital | UPMC Hamot                  | UPMC Northwest      |
| Meadville Medical Center           | UPMC Horizon                | UPMC Passavant      |
| Conemaugh Memorial Medical Center  | UPMC Jameson                | UPMC Presbyterian   |
| St. Clair Hospital                 | UPMC Magee Women's Hospital | UPMC Shadyside      |
| UPMC Altoona                       | UPMC McKeesport             | UPMC St. Margaret   |
| UPMC East                          | UPMC Mercy                  | Washington Hospital |
| Heritage Valley Beaver             | Heritage Valley Sewickley   |                     |

## Randomization Procedure

The study will use web-based randomization to one of the five care models for those individuals who consent to participate in the study. Once a research coordinator determines eligibility, obtains informed consent, and the patient is discharged to home while maintaining eligibility, he or she will enter in key identification information, and the system will then generate a Study ID (numeric identification number) along with assignment to an intervention arm. Randomization will initially be fixed with 30% of patients randomized to STS and the remaining 70% of patients randomized 1:1:1:1 between the four RPM care models. After 250 patients have been randomized and followed for 90 days, the first interim analyses will be conducted and RAR will begin and continue to be updated every three months. During the RAR phase, the randomization to STS will remain fixed to be 30% of patients and the remaining 70% of patients will be randomized to one of the four RPM models preferentially based on the probability that each RPM care model is optimal.

While the research coordinators will see each assigned intervention arm per the randomization process, they will be blinded to overall changes in treatment allocation rates. Other study team members, including Principal Investigators, Co-Investigators, statistical analysts, and database administrators will also be blinded to treatment allocation rates during the course of data collection.

## Study Population

Our study population will consist of patients who are UPMC Health Plan members or have Medicare Fee-for-Service insurance age 21 and older hospitalized with a primary diagnosis of sepsis or lower respiratory tract infection, who are discharged to home (from the hospital or after a SNF stay of 28 days or fewer), and are at moderate- or high-risk for readmission.

## Inclusion/Exclusion Criteria

### 1. Inclusion criteria

- a. UPMC Health Plan member or patient with Medicare Fee-for-Service insurance
- b. Treated at a prespecified hospital for sepsis or lower respiratory tract infection
- c. Age 21 or older
- d. Medium or high risk of readmission

### 2. Exclusion criteria

- a. Admitted from setting other than home, independent living, or personal care home
- b. Receiving hospice at time of admission
- c. For Health Plan members: being discharged on/to hospice, Inpatient Rehabilitation, long-term acute care hospital, or assisted living facility
- d. For Medicare Fee-for-Service enrollees: being discharged on/to hospice, Inpatient Rehabilitation, long-term acute care hospital, skilled nursing facility, or assisted living facility
- e. Currently participating in UPMC Advanced Illness Care program
- f. Unable to participate in RPM due to lack of technology/internet connection
- g. Known Pregnancy
- h. Severe, persistent cognitive impairment
- i. PCP disapproves of patient being in remote patient monitoring program
- j. No PCP available to participate
- k. Patients who are discharged from hospital to skilled nursing facility and stay at the skilled nursing facility for greater than 28 days

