### Domain: Patient-Level:

Patient Demographics and clinical characteristics: We include in our baseline survey questions regarding age, race, ethnicity, marital status, and gender. Insurance type and the Charleston Comorbidity index will be pulled from administrative and claims data at baseline. We will ask questions about generalized anxiety disorder, depressed mood and anhedonia, health literacy, and comfort with technology.

Living at home status: We include in our baseline and 90-day survey questions regarding whether a participant lives at home alone or with others. If participants live with others, an additional question to identify their living companion(s) is asked. The participant can identify multiple living companions from a list.

Payer: Based on literature review and the experience of our study investigators, we do not expect large differences in the distributions of post-discharge home days between UPMC Health Plan and MC FFS study participants. However, in the event that participant payer (UPMC Health Plan or MC FFS) is predictive of home day distribution, randomization of study interventions ensures that effectiveness comparisons are guaranteed to remain unbiased toward any particular arm. Thus, our primary analysis model will remain as it is currently stated in the Statistical Analysis Plan.

To maximize oversight the proposed new subgroup (MC FFS), home days distributions of each payer type group will be reported to the DSMB in regular quarterly interim analysis reports. In addition, we will conduct two types of sensitivity analyses to detect any differences in the two distributions after data collection:

1. We will fit two additional proportional logit models accounting for payer type:
  - a. One logit model including a term for payer which will capture proportional shifts in home days across payer groups; and
  - b. A second model that will include different intercept terms for the payer type groups. This model will capture non-proportional shifts in home days across both groups.
2. We will explore potential differential effects of RPM care models across payer types. One model will estimate interaction terms between RPM arm and payer type; and another will fit separate proportional logit models to UPMC Health Plan and MC FFS participants.

Domain: Socioecological:

Distance to primary care provider (PCP) office: Distance from participant's home address to the PCP office in miles will be pulled from administrative data at baseline.

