#### 4.2.2. Exclusion criteria from this domain

Patients will be excluded from this domain if they have any of the following:

- Admitted from setting other than home or independent living
- Receiving hospice at the time of admission
- Being discharged on/to hospice or LTAC
- Currently participating in UPMC Advanced Illness Care Program
- Unable to participate in RPM due to lack of technology/internet connection
- Known pregnancy
- Severe, persistent cognitive impairment
- No documented primary care physician (PCP)
- PCP disapproves of the patient potentially being enrolled in remote patient monitoring

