#### 8.9.7. Sensitivity analyses exploring the potential impact of payer type

On August 10, 2022 the trial expanded its inclusion criteria to include Medicare Fee-For-Service (MC FFS) patients. We will conduct two types of sensitivity analyses to detect any differences in PDHD distribution between UPMC Health Plan and MC FFS patients:

- We will fit two additional proportional logit models accounting for payer type:
  - One logit model including a term for payer which will capture proportional shifts in home days across payer groups; and
  - A second model that will include different intercept terms for the payer type groups. This model will capture non-proportional shifts in home days across both groups.

- We will explore potential differential effects of RPM care models across payer types. One model will estimate interaction terms between RPM arm and payer type; and another will fit separate proportional logit models to UPMC Health Plan and MC FFS participants. We will also explore limiting these analyses to data collected after August 10, 2022 when MC FFS patients were eligible.

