## 12. Appendix

### 12.1. *Sepsis data for simulations*

To create realistic clinical trial simulations, we obtained pre-trial member-level data from UPMC for patients that were hospitalized from either sepsis, pneumonia, and/or a lower respiratory infection. Patients in this sample were at least 21 years old and deemed low risk for readmission (based on an internal UPMC risk score). We received 4718 records from members that received their insurance through Medicare or commercial plans. This data included the following covariates: age group, CCI, sepsis status, pneumonia status, LRTI status, whether a patient had mechanical ventilation, vasopressors, or was in the ICU. In addition, we have whether a patient was discharged to a SNF or to home, as well as their home days endpoint score. We additionally received 2737 records from members whose insurance is through Medicaid or SNP (special needs population). This data only contained the home days endpoint with no additional covariate information.

Using the totality of this data, we summarize the home days distribution by finding the proportion in each level of the outcome, as shown in the “Overall” column in Figure 2.

In addition, we summarize the two strata variables using the partial data with covariate information. We define the severe strata as patients who were on mechanical ventilation or vasopressors during their hospital stay. In this data, 11% of the population meets this definition. We define the SNF population as patients whose discharge status was “Discharge to SNF”, where 37% of the population meet this definition. Using these covariates, we estimate the relationship between the home days endpoint and the covariates, illness severity and discharge to SNF, using a frequentist ordinal regression. We estimate an odds ratio for severe illness compared to non-severe of 0.75 and an odds ratio for patients discharged to SNF compared to those discharged home to be 0.35. Under these estimated odds ratios, we transform the home days distribution (using the full data) for the severe strata and the discharged to SNF strata. The resulting distributions are presented in Figure 2. Patients who are not categorized as severe or were discharged straight to home are assumed to have the baseline home days distribution shown in the overall column.

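### The protocol bars fee-for-service patients, but not Health Plan members, from entering by way of a SNF, so unadjusted payer summaries and arm-by-payer comparisons partly mix payer with discharge location

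*Combined protocol and SAP*

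**What the plan says.** The protocol's exclusion criteria treat the two payers differently. Criterion (c) reads "For Health Plan members: being discharged on/to hospice, Inpatient Rehabilitation, long-term acute care hospital, or assisted living facility". Criterion (d) reads "For Medicare Fee-for-Service enrollees: being discharged on/to hospice, Inpatient Rehabilitation, long-term acute care hospital, skilled nursing facility, or assisted living facility". Only (d) names a SNF. Criterion (k) then removes anyone whose SNF stay exceeds 28 days.

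The protocol's Study Population section describes patients "who are discharged to home (from the hospital or after a SNF stay of 28 days or fewer", with no split by payer. In the domain-specific appendix, section 4.2.2 has a single discharge exclusion for both payers, "Being discharged on/to hospice or LTAC". The appendix's summary table has the same item and bars only SNF stays over 28 days, again for either payer.

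SNF discharge is one of the two stratum terms in the primary model (Z2 in section 8.3.2). Section 12.1 reports "an odds ratio for patients discharged to SNF compared to those discharged home to be 0.35". For the other stratum it says "We estimate an odds ratio for severe illness compared to non-severe of 0.75".

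Three uses of payer matter here:
- The protocol's Payer paragraph says that "home days distributions of each payer type group will be reported to the DSMB in regular quarterly interim analysis reports".
- Section 8.9.7 adds a payer term in one model and payer-specific intercepts in another.
- Section 8.9.7 also fits arm-by-payer interactions, and "another will fit separate proportional logit models to UPMC Health Plan and MC FFS participants".

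None of these passages mentions that one payer group can contain SNF patients and the other cannot.

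**The concern.** The payer analyses are the plan's main check on the August 2022 decision to admit FFS patients. If the protocol's rule operates, the FFS-by-SNF cell is empty. A payer comparison that ignores discharge location then sets a home-only group against a mixed group, on the stronger of the two prognostic strata.

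Two things are at stake. First, a board looking at distributions by payer could read case mix as a payer effect. Section 8.11.1 makes this harder to untangle. FFS outcomes come from records review, and no record is taken as no event, so missed FFS events would also make that group look healthier. The two explanations push in the same direction. Second, an arm effect that differs between SNF and home patients could be reported as an arm effect that differs by payer.

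Separately, protocol and appendix define different eligible populations, which matters whatever is decided about the analysis.

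**Working it through.** **Inputs.** Home-days distribution for the baseline population: section 12.2, Table 2 (death 0.133, 90 days 0.454; the nine cells sum to 0.999 and were rescaled to 1). Odds ratios 0.35 (SNF) and 0.75 (severe): section 12.1. Severe share 11% and SNF share 37%: section 12.2. Alternative SNF share 500/1,668 = 30%: protocol, Sample Size.

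**Assumptions.** The documents do not give SNF shares by payer, so the trial-wide 30% and 37% are applied to Health Plan members, with 10% as a low case. The FFS share of enrolment is not given either; 10%, 30% and 50% were tried.

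**Step 1: reproduce the plan's figure.** A proportional-odds shift divides the odds of Y ≤ j by the odds ratio.
- SNF, death: 0.1331/0.8669 = 0.1536; 0.1536/0.35 = 0.439; probability 0.305.
- SNF, 90 days: 0.5455/0.4545 = 1.200; 1.200/0.35 = 3.43; probability of 90 days 1/(1 + 3.43) = 0.226.
- Table 4 gives 0.31 and 0.23, and Table 6 gives 0.30 for the same mortality. The figures agree within rounding.
- Severe: 0.170 and 0.384, against 0.17 and 0.38 in Table 4.

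**Step 2: unadjusted payer contrast with no payer effect.** Averaging over 11% severe gives these values:
- Direct-to-home: mortality 0.89 × 0.1331 + 0.11 × 0.170 = 0.137; P(90) = 0.447.
- SNF: mortality 0.89 × 0.305 + 0.11 × 0.369 = 0.312; P(90) = 0.221.

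FFS is all direct-to-home. Health Plan is a mix with SNF share s. For s = 0.30, mortality is 0.70 × 0.137 + 0.30 × 0.312 = 0.190. The odds ratio for survival is (0.810/0.190)/(0.863/0.137) = 0.68. The odds ratio for 90 days is (0.379/0.621)/(0.447/0.553) = 0.76.

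| SNF share in Health Plan | Mortality, Health Plan vs FFS | P(90 days), Health Plan vs FFS | Cumulative OR across cut points |
|---|---|---|---|
| 10% | 15.5% vs 13.7% | 42.4% vs 44.7% | 0.87-0.91 |
| 30% | 19.0% vs 13.7% | 37.9% vs 44.7% | 0.68-0.76 |
| 37% | 20.2% vs 13.7% | 36.3% vs 44.7% | 0.63-0.71 |

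Fitted as a single proportional-odds payer term without Z2, the contrast is 1.37 (30%) or 1.47 (37%) in favour of FFS. That is close to the expected treatment effect of 1.5 in Table 3.

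**Step 3: the same fit with Z2 kept.** The payer odds ratio returns to 1.00 and the SNF odds ratio to 0.35, for every SNF share from 5% to 45% and every FFS share tried. For SNF shares of 30-37%, the payer-SNF correlation is -0.20 to -0.48 and the variance inflation factor 1.04 to 1.29. Both main effects are estimable. Only payer-by-SNF is not.

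**Step 4: arm-by-payer with Z2 kept.** This uses an FFS share of 30%, the RPM arms pooled at 70% against STS at 30%, and no true payer modification.

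| Arm OR at home / in SNF (assumed) | Arm-by-payer OR, SNF share 30% | SNF share 37% |
|---|---|---|
| 1.5 / 1.5 | 1.00 | 1.00 |
| 1.5 / 1.0 | 1.14 | 1.17 |
| 1.0 / 1.5 | 0.88 | 0.86 |

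In the second row at a 30% share, the arm odds ratio is 1.32 in Health Plan members and 1.32 × 1.14 = 1.5 in FFS.

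**The case against.** A reader might infer that payer is aliased with SNF and that all the planned payer comparisons are confounded. The documents do not support that. Health Plan members discharged directly home exist, so the two effects separate (step 3). The base model already contains Z2, and section 8.9.7 describes its payer models as additions to it. If Z2 is kept and its effect is proportional, the payer main effect is clean. The text implies that Z2 stays but does not say so.

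The other points against are fair, and most stand in part.
- No adaptation, futility or success rule uses payer, so the DSMB display is oversight only. Its layout is not given, and a further split by stratum is not ruled out.
- The 0.35 comes from all pre-trial patients with a SNF discharge status, in a sample described as low risk for readmission and with no 28-day limit mentioned. The trial randomizes on discharge home and excludes longer SNF stays, so the gap among participants may be smaller.
- The arm-by-payer artefact needs an arm-by-SNF difference, and section 8.3.2 assumes there is none. Even under the assumed contrast it is small against the noise. With 1,281 × 0.975 = 1,249 complete patients and 30% FFS, the standard error of the log interaction is about 0.25 with the RPM arms pooled and 0.34 for one arm. The artefact of log 1.14 = 0.13 to log 1.17 = 0.16 is then about 0.4 to 0.6 standard errors.
- Section 8.10.2 already plans an arm-by-discharge-location analysis, so the rival explanation will be visible. But listing it there also concedes that such a difference is plausible, and section 8.9.7 does not link the two.
- The Study Population wording can be read as a summary that the exclusions narrow. The appendix's exclusion lists cannot be read that way.

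**Conclusion.** The concern holds in a limited form. The exclusion lists conflict between protocol and appendix. If the protocol's criterion (d) operates, payer is partly confounded with SNF discharge.

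Unadjusted payer distributions would then differ by a cumulative odds ratio of about 0.63-0.76 with no payer effect. This rests on the planning SNF shares of 30-37% and the pre-trial odds ratio of 0.35; at a 10% share it is 0.87-0.91. The payer main effect in section 8.9.7 is safe from this if Z2 is kept and odds are proportional. The arm-by-payer and separate-payer results are safe only if arm effects do not differ by SNF. If they do, keeping Z2 does not help, and the separate FFS fit describes direct-to-home patients only.

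The randomized arm comparisons and the primary analysis are not biased by any of this. It is a cheap improvement to the sensitivity analyses and the DSMB report, not a flaw in the trial's main inference.

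**What to change.** 1. Reconcile the SNF rule for FFS patients across the protocol's Study Population and exclusion criteria, the appendix's summary table and section 4.2.2.
2. If criterion (d) stands, show the DSMB payer distributions by discharge location, with SNF participants as a separate row that contains Health Plan members only.
3. State in section 8.9.7 that Z2 stays in the payer-term and payer-intercept models. Restricting those two models to direct-to-home patients is not needed.
4. Run the arm-by-payer interaction and the separate-payer models in direct-to-home participants as well, including in the planned restriction to data after August 10, 2022. Base any claim of payer effect modification on that run.

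The cost is a few sentences in the SAP and DSMB report template plus one data filter. The direct-to-home run loses the Health Plan SNF patients, about 30-37% of Health Plan members on the planning shares, so it is less precise. The primary analysis does not change.

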### *Unanticipated Enrollment in UPMC Advanced Illness Care Program*

The UPMC Advanced Illness Care (AIC) Program is a 6-month palliative care program offered by UPMC Health Plan to members in need of palliative care. Referrals to this program are made both at hospital discharge and during the course of routine outpatient care.

It is rare but possible for a randomized ACCOMPLISH participant to be enrolled into the UPMC Advanced Illness Care (AIC) Program. The Co-Enrollment Workflow is a detailed process designed to prevent this issue; however, co-enrollments are still possible due to organizational complexity and care process variation.

In the event that a randomized ACCOMPLISH participant is also enrolled in the AIC program, the study team will follow a strict intent to treat study design and continue to collect outcomes data per the established timelines and processes. If the number of randomized participants is greater than 10 at the end of all recruitment and data collection, a sensitivity analysis will be performed to determine if the AIC participants have significantly different outcomes than the participants enrolled in the study as planned.

### **Potentially Eligible Patient Dashboard Identification and Chart Review Process:**

Potential participants are initially identified through a dashboard populated daily with inpatient data pulled from an UPMC's electronic health record system. This dashboard shows the medical record number of inpatients who meet some ACCOMPLISH study inclusion criteria such as hospital, age, insurance type, readmission risk score (derived from a predictive model), and pre-specified diagnostic indicators suggestive of sepsis and lower respiratory tract infection (antibiotics ordered for at least two days and at least one culture ordered within the first three days of a hospital stay). The RCs examine the medical records of patients identified on the dashboard for further eligibility criteria including where a patient was admitted from, their planned discharge location (home, SNF, hospice, etc), pregnancy

status, and specific diagnostic indicators of sepsis or lower respiratory tract infection. The table below shows standard criteria found in medical records to use as a guideline determine if an RC can independently deem the patient clinically eligible for the study, or if a clinically-trained PI/Co-I needs to review the patient's chart to confirm clinical eligibility.

| Condition                                | Criteria used by research coordinator                                                                                                                                                                                                                                                                                                                                                                                                                                                                                                                                                                                                                                                                                                                                                |
|------------------------------------------|--------------------------------------------------------------------------------------------------------------------------------------------------------------------------------------------------------------------------------------------------------------------------------------------------------------------------------------------------------------------------------------------------------------------------------------------------------------------------------------------------------------------------------------------------------------------------------------------------------------------------------------------------------------------------------------------------------------------------------------------------------------------------------------|
| Lower respiratory tract infection | All three criteria were met: 
 
Received at least two days of antibiotics, which were started within 24 hours of hospital presentation
 
At least one culture from blood or lower respiratory tract ordered within first three days of hospital presentation
 
Pneumonia or chronic obstructive pulmonary disease (COPD) exacerbation considered as a potential diagnosis
 
                                                                                                                                                                                                                                                                                                                                        |
| Sepsis                            | All three criteria were met: 
 
Clear source of infection (e.g., urinary tract infection, catheter-related blood stream infection, abscess) OR at least one culture (e.g., blood, urine, lower respiratory tract) ordered within the first three days
 
Received at least two days of antibiotics, which were started within 24 hours of hospital presentation
 
At least one criterion for organ dysfunction or notes mentioned "sepsis" or "septic shock": 
 
Elevated serum creatinine and blood urea nitrogen levels (kidney function)
 
Elevated serum lactate levels
 
Received vasopressors (e.g., dobutamine, norepinephrine, epinephrine)
 
 
 
 |
| COVID-19                          | All three criteria were met: 
 
COVID-19 was the primary reason for hospital admission
 
Presence of respiratory symptoms (e.g., shortness of breath, cough dyspnea)
 
Prescribed/ordered one of the following during hospitalization: 
 
Dexamethasone (6 mg daily)
 
One of the following: Remdesivir, Sotrovimab, Bebtelovimab, Paxlovid (nirmatrelvir tablets and ritonavir tablets, co-packaged for oral use), Tocilizumab, Baricitinib
 
Received vasopressors, high-flow oxygen, invasive or non-invasive mechanical ventilation
 
 
 
                                                                                                            |

